### Voice Message Development

We used an exploratory qualitative study design to hear patient and PE perspectives on NCD management and mHealth. We used the 32-item checklist Consolidated Criteria for Reporting Qualitative Research [20] to guide our study design, data collection, analysis, and reporting of our research study. The Information-Motivation-Behavior theoretical framework was used to guide mHealth message development [21] based on providing accurate information, personal motivation, and social motivation to impact behavioral change in chronic disease self-management. We conducted focus groups (N=59) in Khmer with MoPoTsyo patients at 6 ODs within the study territory (Kampong Speu, Chamkar Leu, Baray-Santuk, Stoong, Kong Pisey, and Phnom Penh) to better understand the content of messages that would be most effective and provide guidance on logistics for sending them. Focus groups were held at community Health Centers and lasted for approximately 1.5 hours each. Focus group discussions were audiorecorded with participant permission. For the message content, the focus groups discussed current activities for managing NCDs (eg, medication use, doctor’s visits, lab tests and monitoring, PE groups, and lifestyle changes in diet, physical activity, smoking, and alcohol use), as well as facilitators and barriers to these activities. For the message format, questions included the frequency and duration of messages, preference for text or voicemail format, access to cell phones, the best time of day to send, and ability to respond to a text. At each district, 2 PEs (convenience sample) were also interviewed to evaluate features of the tablet for tracking their patients, to provide outreach and assure usability.

**Figure 1 figure1:**
[figure not shown]
Study design of the project. BP: blood pressure; InSTEDD: Innovative Support to Emergencies, Diseases and Disasters.

The taxonomy of behavioral change communication deemed most appropriate for our intervention can be best described by the Behaviour Change Wheel [22] using the following: sources of behavior of psychological capability, reflective motivation, and automatic motivation; intervention functions of education, persuasion, incentivization, and enablement; and policies driven by communication, marketing, and service provision.

### Voice Message Implementation

We are contracting with experts at Innovative Support to Emergencies, Diseases and Disasters (InSTEDD) Southeast Asia to develop and implement the mHealth app for sending targeted phone messages to MoPoTsyo patients. The app “Verboice” is being used to access the information available in the MoPoTsyo database to tailor messages according to the specific characteristics of patients’ disease. Verboice is a free and open-source tool developed by InSTEDD that runs apps through voice, allowing users to listen and record messages in their own language. At the time of informed consent, patients provided 2 current cell phone numbers, their own plus a backup belonging to a family member. Following the development of specific content for message themes identified in the focus groups, electronic capture of data provided by the PEs will allow us to match the specific issues and needs related to hypertension and diabetes management and send relevant messages to individual patients.

### Outcomes

Process outcomes will follow guidelines of the RE-AIM Model [23] to include Reach (how representative is the sample to the targeted population?), Effectiveness (clinical and intermediate outcomes), Adoption (uptake, utilization, and initial implementation), Implementation (fidelity including adherence and delivery), Maintenance (sustainability), as well as acceptability (satisfaction with the intervention). Key clinical outcomes will include control of blood pressure and glucose, medication adherence, use of medical services (laboratory and physician office visits), and improvement in lifestyle factors such as smoking, body mass index, diet, and exercise. Comparisons will be made by the study intervention group at the end of the trial and by changes in clinical outcomes pre- and postintervention period. Furthermore, comparisons will be made for message effectiveness to determine whether certain message topics led to better clinical outcomes.

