**Methods:**

The study design is a cluster randomized controlled clinical trial randomizing each of 75 Community peer educators (PEs), trained and coordinated by MoPoTsyo Patient Information Center in Phnom Penh, into one of 3 groups of 25 (approximately 60 patients each) to receive either tablet+messages, tablet only, or no intervention (control). The total sample within each group includes 25 clusters and approximately 1500 patients located in 7 Operational Districts in rural regions or urban slums in Cambodia. The interventions (groups 1 and 2) were compared with usual PE monitoring without the tablet or mHealth messaging interventions. Focus groups and informant interviews were conducted to develop messages according to specific themes—medications adherence, laboratory testing, physician visits, obesity, smoking, and general lifestyle issues. Using the data received at monthly PE monitoring meetings, patients will receive specific messages based on their individual health challenges. Following the intervention completion, clinical and process outcomes will be compared with baseline metrics between groups.

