### Approach

In this study, we are collaborating with MoPoTsyo Patient Information Center to enhance their Peer Educator Network model through the application of mHealth-tailored phone messaging and improved eHealth communication throughout the system. A focus on hypertension, justified by the extremely low medication adherence of hypertensive patients compared with diabetic patients, shifts the intervention to an area of great need. Two interventions will be tested, one at the PE level and one at the patient level. The first includes providing electronic tablets to PEs for data collection and transfer to the MoPoTsyo database in Phnom Penh. The tablets are intended to speed up data collection and entry, reduce paper, increase accuracy, and eliminate lengthy distances that must be traveled to bring paperwork to MoPoTsyo. In addition, the tablets will allow PEs to scan a patient’s record “handbook” (log kept with the patient) to be verified by MoPoTsyo quality control staff should data appear suspicious. At the patient level, voice messages developed to address specific patient problems (eg, uncontrolled blood pressure or glucose, medications not picked up at the pharmacy, weight gain, etc) will be sent to patients based on the data received from the monthly visits to the PE. This study has randomly selected 75 PEs for assignment to 1 of 3 intervention groups—tablet+messaging, tablet only, or control (no tablet or voice messages). Figure 1 shows the study design. As we estimate that each of the 25 PEs in each group monitors about 60 patients, each arm of the study will include about 1500 participants for a total community sample of about 4500.

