#### Statistical Analyses

Statistical analysis will be performed collaboratively between Cambodian collaborators and the University of Washington to provide experience to them in this activity. All outcomes, both process and clinical, will be described as N (%) or mean (SD) for categorical and continuous data, respectively. Changes in primary study outcomes, including blood pressure, fasting glucose, and medication adherence, will be calculated as the difference from the baseline to 12-month follow-up. We will evaluate study results 3 ways—first as an intention-to-treat comparison of study outcomes associated with patients in the intervention group versus the control group compared by a change in PE overall clinical outcomes for their patients (mean blood pressure, fasting glucose, and medication adherence). In addition, we will conduct an efficiency analysis using linear regression for the study outcomes evaluating group assignment, as well as other variables, calculated at the PE level (ie, % women, mean education, etc). Finally, we will analyze data at the patient level using Generalize Estimating Equations for each outcome evaluating group assignment and clustering data on PE. Primary dependent variables will include changes in the 3 pre and post continuous clinical outcomes—systolic and diastolic blood pressure, fasting blood glucose, and medication adherence as an intermediate outcome. Covariates will include demographics, baseline clinical values, and urban or rural residency of patients. In these analyses, we will use complier-average causal effects (CACE) to look at the efficacy and effectiveness of the mHealth intervention, which takes the clustering effect of PEs, as well as response of patients into consideration. In these patient-level models, we will conduct an intention-to-treat analysis to evaluate the total causal effect of assigning a PE to the mHealth intervention, regardless of compliance. CACE will also allow us to estimate the mHealth intervention’s effectiveness on patient compliers, considering phone messages received and listened to. In CACE, actual treatment received (compliance to the mHealth treatment) becomes a postrandomized variable and effectiveness based on process outcomes (reach and compliance) are addressed. Analyses will be performed using STATA (StataCorp College Station). No interim analyses are planned.

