## Results

Results of the qualitative research were used to develop the telephone messages according to 6 themes—medications adherence, laboratory testing, physician visits (either annual or for alert determined at PE visit), obesity and weight gain, smoking, and general lifestyle issues (diet, exercise, salt intake, etc). Based on the identified facilitators and barriers, the messages are designed to provide education, motivation, and reminders to help support self-management and address obstacles. Specific scripts were tested with patients and recorded in Khmer by a professional recording studio (Women’s Media Center of Cambodia) using music and voice intonations suggested by advisors.

An algorithm was developed to identify patients needing specific content messages based on the most recent data that were sent electronically to the MoPoTsyo database by the PEs. The delivery of messages was decided according to focus group suggestions, including the use of voicemails rather than text, sending messages at dinnertime or shortly afterward so that a person is at home and can share with family members, limiting frequency to 2-3 messages per week, and eliminating interactive requirements owing to limited access to smartphones and lower cell phone literacy in many rural communities. Results of Verboice tracking allows us to determine which messages successfully reached patients (for later efficacy analyses) and allows the system to send messages additional times when not initially completed.

The focus groups and informant interviews used to develop the mHealth messages were completed during the Spring of 2017. Results of this qualitative work were used to develop the mHealth messages, which were then tested over the summer. Following several revisions of content wording, music, and messenger voice, messages were finalized in July 2017 after which InSTEDD provided channels for delivery of specific themes of message to patients identified by PE data. While the implementation was originally scheduled for 6 months from September 2017 to March 2018, the period was extended 4 additional months because of budgetary efficiencies. Data are currently being cleaned and analyzed. We project that we will have results by Spring 2019.

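### Effects of message topics are to be inferred although each topic is sent because of the patient's own data, so topic effect cannot be separated from the reason for sending

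*Protocol article*

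**What the plan says.** The Outcomes section first describes comparisons by study group, at the end of the trial and as change over the intervention period. It then adds that "comparisons will be made for message effectiveness to determine whether certain message topics led to better clinical outcomes". It names no comparator, outcome scale or model for this second aim.

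Other sections fix how a patient comes to receive a topic:
- **Abstract, Methods:** "patients will receive specific messages based on their individual health challenges".
- **Approach:** the intervention consists of "voice messages developed to address specific patient problems", with the examples "uncontrolled blood pressure or glucose, medications not picked up at the pharmacy, weight gain, etc".
- **Results:** "An algorithm was developed to identify patients needing specific content messages based on the most recent data that were sent electronically" to the central database. Six message themes are listed there.

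Study Setting and Approach make the PE the unit of randomisation, with three arms. No section randomises topics.

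Statistical Analyses gives arm comparisons at PE level, patient-level GEE models for group assignment, and complier-average causal effects for messages received and listened to. For the primary outcomes, change "will be calculated as the difference from the baseline to 12-month follow-up".

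**The concern.** The aim is causal: it asks what topics brought about. Yet the topic a patient receives is decided by the patient's own recent state, often on the same variable, or a close relative of it, that will be used to judge the topic. Patients sent a given topic differ systematically from those not sent it, whether or not the message does anything.

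The stated methods do not deal with this:
- The arm models estimate one contrast, messaging against no messaging. They say nothing about single topics.
- The complier-average analysis rests on that same randomised contrast and treats messaging as a whole. One randomised contrast cannot separate the effects of six themes.
- The baseline covariates are listed for the group-assignment models. Even if carried over to topics, they would account for the trigger only if the trigger were the baseline reading. The algorithm uses the most recent data.

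At stake is the ranking of topics. The article intends its results to support recommendations to the Ministry of Health, so a false ranking could decide which messages are kept.

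**Working it through.** The plan gives no figure for the topic comparison; the figures under Power concern the arm comparison. The check therefore asks what a comparison by topic would show if no message had any effect.

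**Inputs.** From the article: monthly readings, topics assigned from the most recent data, and change measured from baseline to 12 months. Assumed, because the article gives none of these: systolic pressure normal with mean 135 and SD 18, trigger at 140, the same correlation ρ of 0.5 to 0.7 between any two readings, and zero message effect.

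**Constants.** c = (140 − 135)/18 = 0.278, φ(c) = 0.3838, 1 − Φ(c) = 0.3906.
- Flagged patients average φ/(1 − Φ) = 0.3838/0.3906 = 0.983 SD above the mean on the triggering reading.
- Unflagged patients average φ/Φ = 0.3838/0.6094 = 0.630 SD below it.

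**Trigger on one later reading.**
- End gap, flagged minus unflagged: ρ × 18 × (0.983 + 0.630) = ρ × 29.03, which is 14.5 mmHg at ρ = 0.5 and 20.3 at ρ = 0.7.
- Change from baseline: 0 in both groups, because baseline and end readings are equally correlated with the triggering reading.
- Baseline-adjusted gap: with flagged share p = 0.3906, √(p(1 − p)) = 0.4879 and r = ρ × 0.3838/0.4879, the regression coefficient is r(1 − ρ)/(1 − r²) × 18/0.4879. At ρ = 0.5, r = 0.393 and the gap is 8.6 mmHg; at ρ = 0.7, r = 0.551 and it is 8.7.
- Change from the triggering reading in flagged patients: −(1 − ρ) × 18 × 0.983, which is −8.8 mmHg at ρ = 0.5 and −5.3 at ρ = 0.7. This is regression to the mean alone.

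**Trigger on the baseline reading itself.** Change from baseline is −8.8 v +5.7 mmHg at ρ = 0.5 and −5.3 v +3.4 at ρ = 0.7. The positive figures are (1 − ρ) × 18 × 0.630.

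**Trigger on any of ten later monthly readings** (simulation, 600,000 patients), set beside the other cases:

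| Trigger | Change from baseline, flagged v unflagged | End gap | Baseline-adjusted gap |
|---|---|---|---|
| Baseline reading only | −8.8 v +5.7 to −5.3 v +3.4 | 14.5 to 20.3 | about 0 |
| One later reading | about 0 v 0 | 14.5 to 20.3 | 8.6 to 9.0 |
| Any of ten later readings | about 0 v 0 | 20.2 to 23.7 | 12.2 to 10.7 |

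All entries are in mmHg, and ranges cover ρ = 0.5 to 0.7. The adjusted gap of 9.0 arises at ρ = 0.6, by simulation.

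**The zero change depends on equal correlations.** If the triggering reading correlates ρ_B with baseline and ρ_F with the end reading, the change in flagged patients is (ρ_F − ρ_B) × 18 × 0.983. With 0.5 and 0.7 in either order this is ±3.5 mmHg.

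**Check of the remedy.** Under zero effect, comparing randomised halves among patients meeting the same trigger gives differences of at most about 0.1 mmHg, which is simulation noise.

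**The case against.** The strongest reply is that the article condenses a fuller plan. The topic comparison is one supplementary sentence without a stated method, and a comparison of equally flagged patients across arms is not excluded. That is fair as far as missing detail goes. It does not remove the problem, because the article itself states both the causal aim and the assignment rule that defeats a simple comparison by topic, and none of its stated methods bridges the two.

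A reader might infer four stronger things, which the documents do not support:
- **That the topic result will simply be regression to the mean, with blood-pressure messages looking effective on change scores.** The spurious 5 to 9 mmHg fall from baseline arises when the trigger is the baseline reading. With later triggers the stated change score is close to unbiased under equal correlations.
- **That both end values and change scores are planned for topics.** The sentence naming both concerns study groups; the topic sentence names no scale.
- **That regression to the mean affects every topic.** Blood pressure is not itself one of the six themes, and laboratory testing, smoking or general lifestyle messages need not follow an extreme reading. Confounding by indication is the general mechanism.
- **That the trial's main result is affected.** It is not. Arms were randomised, and the topic comparison is not among the primary analyses.

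**Conclusion.** The point holds in this form. As described, a comparison of outcomes by topic received cannot support a statement about what topics caused. It is confounded by the indication for sending, with regression to the mean added where change is counted from the triggering reading.

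Under the assumptions above and later monthly triggers, the spurious gap is about 15 to 24 mmHg in end values and 9 to 12 mmHg after baseline adjustment. Both make the topic look harmful. Unadjusted change from baseline is near 0. Only with a baseline trigger does that change favour the topic, at −5 to −9 v +3 to +6 mmHg. These sizes are illustrative, since the article gives no mean, SD, threshold or correlation. That topic and indication are tied together follows from the article alone.

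This is a secondary analysis that should be corrected. It is not a threat to the primary comparison.

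**What to change.** Data from the tablet-only arm reach the same database electronically (Approach; Electronic Data Capture), so the existing algorithm can be run on them without sending anything. Then:

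1. For each topic, compare tablet+messages with tablet-only among patients whose data first trigger that topic. Count follow-up from the trigger date, analyse by intention to treat and cluster on PE.
2. Include all registered patients of the PEs in both arms, consented or not. Human Subjects Approval describes written consent for message recipients and a waiver elsewhere, so restricting one arm to consenters would undo the balance.
3. A first trigger of one topic may follow messages on another. Use either the patient's first trigger of any topic, or triggers from data collected before messaging began.
4. Report the results as exploratory. Each contrast estimates the effect of the messaging programme in patients first flagged for that topic, since further topics may follow.
5. Label any comparison across topics among recipients as descriptive, and remove the causal wording from that sentence in Outcomes.

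The cost is one further run of an existing algorithm on data already held, and modest programming. The downside is that topic-specific subsets are smaller, so estimates will be imprecise. If this is not done, step 5 alone is the minimum.

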### Data Management

Data collected by PEs during the pilot study will be entered into the tablet at their homes and will be transferred electronically to the newly enhanced Patient Information System database at MoPoTsyo headquarters. The collected data will be stored on a relational database management system and will be securely backed up to an offsite data center affiliated with MoPoTsyo. All data, however, will become a part of the patients’ medical record for longitudinal tracking and access to clinical staff. These data will be available for inclusion in individual, as well as combined, data reports that are a part of the proposed information system.

All data will be monitored by a trained information techinology staff funded under the program dedicated to overseeing data. He will check for missingness and consistency using preprogrammed algorithms to identify problems. After cleaning, data to be analyzed for outcomes will be deidentified and formatted into analytic files for use by coinvestigators and analysts for evaluation.

### Data Analysis

#### Qualitative Analysis

Audiorecordings from the focus group discussions will be transcribed and translated into English. A subset of transcripts will be back-translated to assure accuracy. The transcripts will be analyzed thematically according to the grounded theory approach. Analysis and interviewing will proceed concurrently so that participant responses and emerging themes can shape future focus group discussions and interviews. A coding scheme will be developed on the basis of the topic guide and emerging themes from the transcripts. Two researchers will independently code all transcripts and compare results. Any discrepancies in coding will be discussed and resolved by the research team. Results will be used to inform researchers of the content of messages within the mHealth app and improve the protocol for the introduction of eHealth communications within this project.

#### Statistical Analyses

Statistical analysis will be performed collaboratively between Cambodian collaborators and the University of Washington to provide experience to them in this activity. All outcomes, both process and clinical, will be described as N (%) or mean (SD) for categorical and continuous data, respectively. Changes in primary study outcomes, including blood pressure, fasting glucose, and medication adherence, will be calculated as the difference from the baseline to 12-month follow-up. We will evaluate study results 3 ways—first as an intention-to-treat comparison of study outcomes associated with patients in the intervention group versus the control group compared by a change in PE overall clinical outcomes for their patients (mean blood pressure, fasting glucose, and medication adherence). In addition, we will conduct an efficiency analysis using linear regression for the study outcomes evaluating group assignment, as well as other variables, calculated at the PE level (ie, % women, mean education, etc). Finally, we will analyze data at the patient level using Generalize Estimating Equations for each outcome evaluating group assignment and clustering data on PE. Primary dependent variables will include changes in the 3 pre and post continuous clinical outcomes—systolic and diastolic blood pressure, fasting blood glucose, and medication adherence as an intermediate outcome. Covariates will include demographics, baseline clinical values, and urban or rural residency of patients. In these analyses, we will use complier-average causal effects (CACE) to look at the efficacy and effectiveness of the mHealth intervention, which takes the clustering effect of PEs, as well as response of patients into consideration. In these patient-level models, we will conduct an intention-to-treat analysis to evaluate the total causal effect of assigning a PE to the mHealth intervention, regardless of compliance. CACE will also allow us to estimate the mHealth intervention’s effectiveness on patient compliers, considering phone messages received and listened to. In CACE, actual treatment received (compliance to the mHealth treatment) becomes a postrandomized variable and effectiveness based on process outcomes (reach and compliance) are addressed. Analyses will be performed using STATA (StataCorp College Station). No interim analyses are planned.

